### Statistical methods

#### Statistical methods for primary and secondary outcomes {20a}

Hereby provided is a summary of the most important statistical analyses. Further details will be outlined in the SAP that will be finalized before database lock.

This open-label controlled randomized trial tests a superiority hypothesis with a two-sided type I error rate of 0.05. Secondary hypotheses of this exploratory study will be tested in a non-hierarchical way. These will be described according to the appropriate summary statistics (e.g., proportions for categorical data, means with 95% confidence intervals for continuous data, median for time-to-event data).

The primary outcome is based on an ordinal severity scale with 7 categories. This scale has been proposed by the WHO for COVID-19-related research and has been previously used in trials of patients with influenza. Previously reported studies and ongoing studies record the same primary outcome, which allows cross-study data pooling. The primary endpoint will be analyzed by means of competing risk analyses whereby death without any improvement will be considered as a competing risk. Event rates will be estimated using cumulative incidence functions (CIF). Median times to improvement will be calculated by the treatment group. The effect of treatment will be assessed by performing a Fine and Gray competing risk regression model that includes the baseline value on day 0 as a covariate and randomized treatment as a factor. From the Fine and Gray model, the subdistribution hazard ratio and associated 95% confidence interval will be estimated.

Secondary endpoints will be analyzed as follows:
Cumulative clinical status up to day 15 will be analyzed using a general linear model adjusted for clinical status on day 0. The treatment effect will be estimated by the difference of mean values between the groups.Cumulative clinical status recorded daily during the hospital stay and on days 15 and 19 will be analyzed by means of a proportional odds logistic regression model, adjusted for clinical status on day 0. The treatment effect will be estimated by the common odds ratio.All-cause mortality rates will be estimated by treatment group using the Kaplan-Meier method. The resulting Kaplan-Meier curves will be compared using a log-rank test. The treatment effect will be estimated by the hazard ratio using a Cox regression.Other time-to-event parameters with competing risk: event rates will be estimated using cumulative incidence functions (CIF), and the resulting CIF curves will be compared using Gray’s test. The treatment effect will be estimated by the subdistribution hazard ratio.Duration of hospital and ICU stay: both parameters will be analyzed as time-to-event parameters with competing risk, whereby the event of interest is discharge from hospital/ICU and the competing risk is hospital/ICU death.Continuous normally distributed variables (e.g., QTc) will be analyzed using a 2-sample *t* test. Treatment effects will be estimated by the difference in mean values between the groups. If applicable, changes from baseline will be calculated. Comparisons between treatment groups will be done by performing an analysis of covariance (ANCOVA) on the post-baseline value, using the baseline value as a covariate.Continuous non-normally distributed variables (clinical status, NEWS score, duration of supplemental oxygen, duration of mechanical ventilation) will be analyzed using a Wilcoxon rank-sum test. Change in ordinal scale at specific time points will be compared using Wilcoxon rank-sum tests.

New treatment options in the DAWn consortium have not been added as new treatment strata until now, but are being run as parallel studies. However, the design is still adaptive in that standard of care treatment may change according to the latest evidence. We refrained of defining a standard of care for participating centers, but encouraged them to adhere to the national guidelines. Still final decision about standard of care is left at the clinician’s discretion. For differences between centers, or new recommendations for standard care, statistical adjustments will be made in the analysis.

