#### Sample size {14}

As in other COVID trials [20], the time to reach a 2-point improvement on the WHO ordinal scale was chosen as the primary outcome. While azithromycin is generally safe, some concerns have been raised with the large-scale use in COVID-19, e.g., a possible increase of cardiac adverse events when combined with other QT-prolonging drugs such as hydroxychloroquine or increased bacterial resistance. While the exact proportions of such harms are not yet clear, we deemed that a sufficiently low number needed to treat was necessary to outweigh these potential risks and for the trial results be truly clinically meaningful. An absolute risk difference of 15 to 20% (correlating to a single-digit number needed to treat [NNT] between 7 and 5) therefore seemed appropriate. In concrete clinical terms, this means the following: Based on the control group of the Lopinavir-Ritonavir trial of Cao et al. [20] that used the same ordinal scale and had a similar population, we can assume a 2-point improvement on the ordinal scale will be observed in 40% of patients with standard of care at day 15. An absolute risk difference of 15% or 20% means that respectively 55% or 60% instead of 40% will have reached the primary endpoint in the azithromycin-treated group at day 15.

Based on the log-rank test, with a 2-sided significance level of 5 and 80% statistical power and using a (2:1) randomization ratio in favor of azithromycin, a total sample size of 354 patients would suffice to detect an absolute risk difference of 15%. To detect an absolute risk difference of 20%, a total sample of 196 patients would suffice. We propose a pragmatic sample size of 282 patients taking into account early dropouts. Two hundred fifty-eight patients will be sufficient to detect an absolute improvement of 17.5% with a statistical power of 80% at a 2-sided significance level of 5%.

Although it should be balanced against potential harms, we acknowledge that a larger NNT might also still be clinically relevant due to the scale of the pandemic. This emphasizes the importance of adhering to internationally promoted outcome measures like the WHO ordinal scale, to facilitate data pooling afterwards.

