Over time, increased experience and new treatments may improve outcome with standard of care. In this rapidly changing context, it is impossible to predict all these individual changes. Rather, a period effect will be corrected for by dividing the recruitment period in distinct intervals and correcting all analyses for these intervals. The choice of cutoff dates between the periods will be made during a blind review meeting prior to database lock. In a time-to-event analysis, such a covariate correction will further increase power, albeit at a cost of larger confidence intervals [21]. As our power calculations are based on absolute risk differences, an improved outcome in the standard of care group has little impact on the clinical relevance of our anticipated results.

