##### Concealment mechanism {16b}

The allocation sequence is generated through the computerized system and is immediately revealed to the investigator when inclusion is confirmed and basic demographics (birth date, sex) are provided.

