#### Methods for additional analyses (e.g., subgroup analyses) {20b}

Subgroup analyses for the primary and selected secondary outcomes will evaluate the treatment effect across the following subgroups: duration of symptoms prior to enrolment, age groups, disease severity at baseline, and comorbidities. A forest plot will display confidence intervals across subgroups. Interaction tests will be conducted to determine whether the effect of treatment varies by subgroup.

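### The primary Fine and Gray model leaves out age, which is known for every patient before allocation: a nearly free efficiency gain is forgone, although the stated 80% power is not wrong

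*Protocol article*

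**What the plan says.** All references are to the protocol article.

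- **Primary model** (Statistical methods for primary and secondary outcomes {20a}): a "Fine and Gray competing risk regression model that includes the baseline value on day 0 as a covariate", plus randomized treatment. The section calls itself a summary and leaves detail to an SAP to be finalized before database lock.
- **Mortality** (same section): Kaplan-Meier curves are compared by a log-rank test, and "The treatment effect will be estimated by the hazard ratio using a Cox regression". No covariate is named.
- **Other adjustments:** Sample size {14} corrects all analyses for recruitment intervals. The end of {20a} promises adjustment for center differences and for new standard-of-care recommendations. Neither mentions age.
- **Age at allocation** (Concealment mechanism {16b}): the allocation is "immediately revealed to the investigator when inclusion is confirmed and basic demographics (birth date, sex) are provided".
- **Age as a subgroup factor** (Methods for additional analyses {20b}): the list is "duration of symptoms prior to enrolment, age groups, disease severity at baseline, and comorbidities".
- **Covariates and power** (Sample size {14}): "In a time-to-event analysis, such a covariate correction will further increase power". The correction meant there is the one for recruitment period, and the sentence goes on to mention wider confidence intervals.

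**The concern.** Leaving a prognostic baseline variable out of a hazard model pulls the estimated hazard ratio towards 1 and lowers the power of the treatment test. Age is an apt covariate here for three reasons. It should be complete, because birth date is needed to obtain an allocation. Treatment cannot affect it. It also does not depend on bedside procedures, whereas the section on collection of baseline parameters lets burdensome study procedures be waived and replaced by the nearest assessment.

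Randomization is blocked within center and not stratified by age, so age balance is left to chance. Of the four subgroup factors, baseline severity has a counterpart in the primary model (day-0 status); age has none. What is at stake is efficiency: how much more the trial could learn from the patients it already plans to recruit.

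**Working it through.** **1. The plan's own figures.** Sample size {14} gives a log-rank test "with a 2-sided significance level of 5 and 80% statistical power and using a (2:1) randomization ratio in favor of azithromycin". For the control arm it says "we can assume a 2-point improvement on the ordinal scale will be observed in 40% of patients with standard of care at day 15". It then states that "a total sample size of 354 patients would suffice to detect an absolute risk difference of 15"%, that 196 suffice for 20%, and that 258 suffice for 17.5%.

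Schoenfeld's formula with p1 = 0.40:

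- HR = ln(1 − p2) / ln(1 − p1)
- events = (1.960 + 0.842)² / [(2/3)(1/3)(ln HR)²]
- N = events / [(p1 + 2·p2)/3]

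For p2 = 0.575: HR = ln 0.425 / ln 0.60 = 1.675; events = 7.849 / (0.2222 × 0.2661) = 132.7; mean event rate = (0.40 + 1.15)/3 = 0.5167; N = 132.7/0.5167 = 256.9.

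| p2 | HR | N computed | N stated | Power at stated N |
|---|---|---|---|---|
| 0.55 | 1.563 | 354.0 | 354 | 80.0% |
| 0.60 | 1.794 | 194.0 | 196 | 80.4% |
| 0.575 | 1.675 | 256.9 | 258 | 80.2% |

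The figures reproduce with no covariate in the calculation.

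**2. Adding age to the primary model.** Simulation with N = 258 (172 vs 86), exponential times and censoring at day 15. The baseline hazards were solved so that the marginal rates stay at the plan's 40% and 57.5% whatever the strength of age. The subdistribution hazard was treated as a Cox model.

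Assumptions not in the document: 35% of patients severe at baseline, with hazard ratio 0.5 for improvement; severe patients older by 0.5 SD; age acting linearly with the hazard ratio per SD shown. Each setting had 3,000 trials, so one power figure has a standard error of about √(0.8 × 0.2/3000) = 0.7 points. The gains compare two models on the same data sets.

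The last column is [(z₂ + 1.96)/(z₁ + 1.96)]², where z₁ and z₂ are the normal quantiles of the two powers.

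| Age HR per SD | Status only | Status + age | Gain (points) | Equivalent extra patients |
|---|---|---|---|---|
| 1.0 | 78.8% | 78.6% | none | none |
| 0.8 | 79.7% | 80.9% | 1.2 | about 3% |
| 0.7 | 80.4% | 83.0% | 2.6 | about 7% |
| 0.6 | 81.3% | 86.6% | 5.3 | about 16% |
| 0.5 | 82.4% | 91.0% | 8.6 | about 30% |

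Example at 0.5: [(1.341 + 1.96)/(0.931 + 1.96)]² = (3.301/2.891)² = 1.30.

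A second simulation, also with status in the model and the same marginal rates, gave gains of about 0 points at 0.8, 4 to 5 at 0.65 and 10 at 0.5. Together: 0 to 1 point at 0.8, 3 to 5 at 0.7 to 0.6, and 9 to 10 at 0.5. With no covariates at all, simulated power was 76% to 78%, slightly below Schoenfeld's approximation.

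**3. Mortality.** The document gives no mortality rates; 20% vs 10% is assumed, with hazard ratio 2.0 for severe status (2,500 trials per setting). Power of the Cox treatment test:

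| Age HR per SD | No covariate | Status | Status + age |
|---|---|---|---|
| 1.5 | 59.4% | 61.4% | 62.6% |
| 2.0 | 60.7% | 62.6% | 65.8% |
| 2.5 | 59.4% | 61.1% | 68.2% |

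About 2 points of each gain come from status rather than age.

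**The case against.** The strongest objection is that the covariate list is not closed. Section {20a} is a summary, the primary-model sentence also omits period and center although both are promised elsewhere, and detail goes to an SAP that is not shown. So the absence of age does not prove that age is excluded. That limits the point but does not remove it: the article names the model terms and the further corrections, age is in neither, and adding it is a specific improvement from a value already collected.

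Four stronger readings are tempting, and the documents do not support them.

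- **That planned power is lost.** A reader who takes 1.675 as the hazard ratio at fixed age, and calibrates only the control arm to 40%, finds unadjusted power of about 71% to day 15 at an SHR of 0.65 per SD. But the treated rate then falls to about 56.4% (55.0% at 0.5), so the difference tested is 16.4 or 15.0 points instead of the planned 17.5. That setup also omits day-0 status, which the plan includes.
- **That the plan itself says age adjustment would add power.** Its remark is about recruitment period. The mechanism carries over to age, but that step is ours. Likewise, the subgroup list concerns effect modification and does not declare age prognostic.
- **That the planned mortality test would gain.** The planned comparison is a log-rank test, which a covariate in the Cox model leaves unchanged. Mortality is secondary and carries no power claim.
- **That the unadjusted ratio is biased.** The randomized comparison is valid without age, and chance imbalance does not invalidate the test. The adjusted ratio is a conditional quantity and lies further from 1 (1.77 vs 1.73 at an age HR of 0.7), so the gap is not simply error removed.

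**Conclusion.** The point stands as a forgone efficiency gain, not as an error. The sample size is correct on its own terms. Adding age to a primary model that already holds day-0 status would gain between nothing and about 10 points of power. The likely size cannot be narrowed further, because the document gives no age effect. The figures also rest on the assumed share and effect of severe disease, its assumed link with age, and follow-up to day 15. The downside is negligible: if age is not prognostic, power is essentially unchanged. For mortality, the gain applies to the Cox estimate and its own test, at assumed event rates.

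**What to change.** In the SAP, before database lock and while the statistician is still blinded:

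- Add age at randomization as a continuous covariate to the primary Fine and Gray model, alongside day-0 status and the adjustments already promised.
- Add day-0 status and age to the Cox model for mortality, and state that the log-rank comparison stays unadjusted.
- State that the adjusted ratios are conditional on these covariates, so that they are not read as the same quantity as unadjusted ratios when data are pooled with other trials.

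The cost is a few lines of SAP text and one degree of freedom for age in each model (the mortality model also takes on day-0 status). No new data are needed, and the sample size does not change. Timing matters: in an open-label trial, a covariate added after outcomes are known would look data-driven.

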### Objectives {7}

The overall objective of the studies of the DAWn consortium is to evaluate the clinical efficacy and safety of investigational therapeutic agents in patients hospitalized with COVID-19. The multicenter DAWn-AZITHRO study will assess the efficacy and safety of azithromycin relative to the standard of care.

The primary outcome of all DAWn-studies will be clinical severity assessed as time to life discharge or to sustained clinical improvement measured according to the WHO master template for clinical studies to allow pooling of the data with other ongoing studies in and outside the consortium.

Secondary outcomes for DAWn-AZITHRO are clinical status and mortality during hospitalization and on days 15 and 29, time to events (ICU, death, discharge), duration of respiratory support, duration of hospitalization, duration of intensive care stay, occurrence of specific cardiac events (QTc prolongation, arrhythmia requiring intervention, reanimation, sudden cardiac death), and safety assessed by cumulative incidence of serious adverse events (SAEs) and adverse events (AEs) graded as grade 4 or 5, discontinuation or temporary suspension of drug administration (for any reason), changes in white cell count, hemoglobin, platelets, creatinine, glucose, total bilirubin, ALT, and AST over time.

Exploratory outcomes will be radiological and various functional evaluations 5–7 weeks post-discharge.

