##### Daily assessments until discharge

Administration of study drugVital signs (National Early Warning Score: BP syst, BP diast, HR, T°C, SPO2 (%), RR, O2 supplement (L/min), AVPU score)Clinical data collection for assessment of study outcomesTargeted medication reviewAdverse event evaluation

Serious adverse event and adverse event grades 4 and 5 will be collected when these are not outcomes of the study. When study-related procedures impose an additional burden on the clinical care of patients, they can be waived.

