##### Visit at days 15 (± 2) and 29 (± 3)

These visits can be phone visits when patients are no longer hospitalized or when safety issues do not permit physical contact. Primary and secondary outcomes are systematically assessed with standardized worksheets provided by the sponsor (complete set of worksheets can be provided on request).

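### The proportional-odds analysis of clinical status names day 19 and the wrong variable, leaving day-29 status without its model, and a rank test is listed beside it with no order between them

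*Protocol article*

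**What the plan says.** All of the analysis text is in the protocol article, under Statistical methods for primary and secondary outcomes {20a}.

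- **Linear model.** The first secondary analysis takes the cumulative clinical status to day 15, adjusts for day-0 status and reports a difference in means.
- **Proportional-odds model.** The next sentence again takes cumulative clinical status as its variable, recorded daily in hospital and "on days 15 and 19 will be analyzed by means of a proportional odds logistic regression model", with adjustment for day-0 status. The effect measure is the common odds ratio.
- **Wilcoxon test of status.** Further down, clinical status appears with the NEWS and the oxygen and ventilation durations in a group of skewed continuous measures, all of which are assigned a rank-sum test.
- **Wilcoxon test of change.** Directly after it: "Change in ordinal scale at specific time points will be compared using Wilcoxon rank-sum tests". The time points are not named.
- **Ranking.** "Secondary hypotheses of this exploratory study will be tested in a non-hierarchical way".

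Other sections fix the days. Objectives {7} lists "clinical status and mortality during hospitalization and on days 15 and 29". The Secondary outcome section gives ordinal status daily in hospital and at the same two days. It lists, as a separate item, a cumulative score that sums the daily values over days 1 to 15. The participant timeline and the visit section ("Visit at days 15 (± 2) and 29 (± 3") schedule contacts on those two days and none on day 19.

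**The concern.** The sentence is an operative analysis rule, and it departs from the rest of the article in both the variable and the day. If a programmer followed it literally, the proportional-odds model would be run on a day when the trial makes no contact with discharged patients. Day-29 status, a defined secondary outcome, would get no analysis with baseline adjustment and a common odds ratio. It would fall only under the Wilcoxon entry.

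Separately, status at a given day is assigned to two methods. One adjusts for baseline and yields an odds ratio. The other, applied to raw status, does neither. Nothing in the section says which result is to be reported as the answer for this outcome.

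**Working it through.** The article states no figure that this point depends on, so the check is mainly a comparison of texts.

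**Step 1: the days.**

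| Place in the protocol article | Days for clinical status |
|---|---|
| Objectives {7} | in hospital, 15, 29 |
| Secondary outcome | daily in hospital, 15, 29 |
| Participant timeline {13} | daily to discharge, 15 ± 2, 29 ± 3 |
| Visit section | 15 ± 2, 29 ± 3 |
| Proportional-odds sentence, {20a} | daily in hospital, 15, **19** |

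The visit windows are 15 − 2 = 13 to 15 + 2 = 17, and 29 − 3 = 26 to 29 + 3 = 32. Day 19 is 2 days after the first window closes and 7 days before the second opens, so no visit deviation could supply it.

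**Step 2: who has a day-19 score.** The section headed "Daily assessments until discharge" provides a score for anyone still in hospital. For a living patient already discharged, the scale distinguishes category 1 (no limitation) from category 2 (limitation), and that needs a contact. The telephone evaluations on days 15 and 29 provide one; nothing does on day 19. A literal day-19 analysis would therefore either be confined to patients still in hospital, a group defined after randomization, or rest on imputed values for those who had gone home.

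**Step 3: the variable.** The cumulative score is a sum over days 1 to 15. It cannot be recorded daily and at a later visit, and it already has the linear model. The proportional-odds sentence otherwise follows the structure of the first secondary outcome, ordinal status daily and at two later days. So the word cumulative does not belong there, and 29 is the natural reading for 19.

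**Step 4: the two methods.** Clinical status falls under the adjusted proportional-odds model and under a Wilcoxon test that takes no covariate. Change in the scale goes to a further Wilcoxon test, which uses baseline only by subtraction. No text orders them.

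**Step 5: an illustration of the overlap.** A simulation with no treatment effect used 188 against 94 patients (282 at 2:1), 600 runs, and assumed distributions for baseline and follow-up status. It compared the Wilcoxon test of raw status with the adjusted proportional-odds model.

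| Result at p < 0.05 | Share of runs |
|---|---|
| Wilcoxon rejects | 4.8% |
| Proportional odds rejects | 4.7% |
| At least one rejects | 6.2% |
| The two verdicts differ | 2.8% |

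The Monte Carlo standard error of the 6.2% is √(0.062 × 0.938 / 600) = 0.0098, about 1 percentage point, so it is not clearly separated from 5%. On these assumptions, any inflation from having two unranked tests is small.

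**The case against.** The strongest reply is that this is an editorial slip. The sentence mirrors the outcome definition except for one digit and one word, several other places fix day 29, and no careful reader would plan a day-19 analysis. The section also describes itself as a summary, with details left to an analysis plan that is not shown. Ranking a main and a sensitivity analysis of a secondary outcome is the kind of detail such a plan usually settles, and reporting a rank test beside an odds ratio is not an error in itself. Most of this stands and is why the point is minor. It does not remove the point, because the published rule contradicts the article's own outcome definition. That is a misstatement, not a missing detail.

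A reader might infer more than the article supports:

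- **That nothing is recorded on day 19.** Inpatients are scored every day until discharge. The gap concerns discharged patients.
- **That the day-29 analysis is wrong by design.** Nothing suggests a deliberate choice. The accurate statement is that day 29 is left without its named model.
- **That the analyst could pick the better p-value after unblinding.** Section 17a keeps the trial statistician blinded until database lock, and {20a} has the analysis plan finalized before lock. If both are followed, the order can be set in time.
- **That the lost precision can be put as a percentage.** Squaring an assumed baseline-to-follow-up correlation is a linear-model approximation. It does not carry over directly to a log odds ratio, and the article gives no correlation.
- **That every Wilcoxon test here ignores baseline.** The test of change uses it by subtraction; only the test of raw status does not.

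**Conclusion.** Wrong as written, and minor. The proportional-odds sentence names the wrong day and the wrong variable, so day-29 clinical status has no named model when the text is taken literally. Status is also given to an unadjusted rank test with no statement of which analysis leads.

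The reach is limited to a secondary, exploratory outcome tested without hierarchy. The primary Fine and Gray analysis is unaffected. No loss of power or precision is claimed. The conclusion rests on comparing the article's own sections; the simulation depends on assumed distributions and serves only to show that the overlap has modest consequences. The analysis plan may already have the correct wording, which cannot be checked here.

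**What to change.** Three wording changes in {20a}:

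1. In the proportional-odds sentence, delete the word cumulative and replace 19 by 29, so that it covers clinical status daily during the hospital stay and on days 15 and 29.
2. State that the proportional-odds model adjusted for day-0 status, with the common odds ratio, is the main analysis of this outcome.
3. Remove clinical status and change in the ordinal scale from the Wilcoxon entries, or keep them labelled as sensitivity analyses with their days named.

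The proportional-odds model is the better choice for the main analysis because the Sample size section promises to correct all analyses for recruitment period. The model can take period as a covariate, whereas a plain rank-sum test cannot.

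The cost is a text correction, carried into the analysis plan before database lock. The baseline score, both visits and the model are already planned, so no new data or patients are needed.

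### Mortality, discharge, ICU and length-of-stay comparisons are stated without day-0 clinical status, although the primary and two other efficacy models adjust for it: an efficiency and consistency gap, not an error

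*Protocol article*

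**What the plan says.** All of this stands in the protocol article, mainly in the section on statistical methods for primary and secondary outcomes {20a}.

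- Primary outcome: a "competing risk regression model that includes the baseline value on day 0 as a covariate and randomized treatment as a factor".
- Cumulative clinical status to day 15: "will be analyzed using a general linear model adjusted for clinical status on day 0". The proportional odds model in the next item carries the same adjustment.
- All-cause mortality: Kaplan-Meier curves, a log-rank test, and "The treatment effect will be estimated by the hazard ratio using a Cox regression". No covariate or stratum is named.
- Other time-to-event outcomes with competing risk: cumulative incidence curves compared by Gray's test, and "The treatment effect will be estimated by the subdistribution hazard ratio". No covariate or stratum is named.
- Hospital and ICU stay: treated as competing-risk times to discharge, again with no covariate named.

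Two general adjustments appear elsewhere. The sample size section {14} promises to correct all analyses for recruitment period, and remarks that covariate correction raises power in time-to-event analyses. The end of {20a} promises adjustment for centre differences and for changes in standard of care. Neither mentions baseline severity.

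**The concern.** The eligibility criteria {10} admit patients ranging from radiographic infiltrates alone to mechanical ventilation. Randomisation is in blocks of 9 within centre, and no stratification by severity is stated. Day-0 status on the 7-point scale is therefore likely to vary widely and to predict death, discharge and length of stay. The protocol treats it as prognostic by adjusting for it in three models.

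Two things are at stake. The first is efficiency: leaving a prognostic baseline variable out of a time-to-event comparison usually costs power. The second is consistency. The primary outcome section notes that, for a patient on a normal ward, a 2-point improvement amounts to discharge. For those patients time to discharge is nearly the primary event, yet the plan would report an adjusted subdistribution hazard ratio for one and an unadjusted one for the other. Because hazard ratios are non-collapsible, the two do not estimate the same quantity.

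**Working it through.** **Step 1: the plan's own sample sizes.** Inputs from the sample size section {14}: "Based on the log-rank test, with a 2-sided significance level of 5 and 80% statistical power", "using a (2:1) randomization ratio in favor of azithromycin", and "a 2-point improvement on the ordinal scale will be observed in 40% of patients with standard of care at day 15". Under proportional hazards:

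- HR = ln(1 − p2) / ln(1 − p1)
- events = (1.960 + 0.842)² / [(2/3)(1/3)(ln HR)²]
- N = events / [(2·p2 + p1)/3], rounded up to a multiple of 3

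| p1 | p2 | HR | Events | Mean event rate | N computed | N stated |
|---|---|---|---|---|---|---|
| 0.40 | 0.55 | 1.563 | 177 | 0.500 | 354 | 354 |
| 0.40 | 0.60 | 1.794 | 104 | 0.533 | 195 | 196 |
| 0.40 | 0.575 | 1.675 | 133 | 0.517 | 258 | 258 |

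The figures reproduce. The total of 282 implies 1 − 258/282 = 8.5% dropout. All of this concerns the primary outcome; the plan states no power for the outcomes at issue here.

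**Step 2: what leaving out day-0 status costs.** The documents do not say how strongly day-0 status predicts these outcomes, so a range is shown. The assumptions, none of them from the documents, are:

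- day-0 mix over categories 3/4/5/6 of 25/55/10/10%;
- exponential times with censoring at day 29;
- discharge: 80% of controls by day 29, conditional HR 1.5;
- death: 20% of controls by day 29, conditional HR 0.5.

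Each scenario used 2,000 trials of 258 patients (172:86), two-sided 5%. The unadjusted log-rank test was compared with a Cox model holding treatment and day-0 category as a linear score. Competing death was not simulated.

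| Outcome | HR per day-0 category | Log-rank power | Adjusted Cox power | Difference (points) | Mean HR, unadjusted / adjusted |
|---|---|---|---|---|---|
| Discharge | 1.0 | 81.1% | 80.3% | −0.8 | 1.50 / 1.51 |
| Discharge | 0.8 | 77.0% | 78.9% | +1.9 | 1.48 / 1.49 |
| Discharge | 0.6 | 70.0% | 79.6% | +9.6 | 1.44 / 1.50 |
| Discharge | 0.4 | 54.8% | 78.6% | +23.8 | 1.35 / 1.51 |
| Death | 1.0 | 54.6% | 53.0% | −1.6 | 0.50 / 0.50 |
| Death | 1.5 | 52.6% | 51.9% | −0.7 | 0.51 / 0.50 |
| Death | 2.0 | 51.9% | 53.0% | +1.1 | 0.52 / 0.50 |
| Death | 3.0 | 46.1% | 55.3% | +9.2 | 0.55 / 0.50 |

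The Monte Carlo error of a single power figure is about √(0.5 × 0.5 / 2000) = 1.1 points, so the death results up to a hazard ratio of 2 per category show no material gain.

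**Step 3: validity.** With no treatment effect, in the discharge scenarios at 0.6 and 0.4 per category, the log-rank test rejected in 4.9% and 5.1% of trials and the adjusted model in 5.7% and 5.4%. The Monte Carlo error here is about √(0.05 × 0.95 / 2000) = 0.5 points. The unadjusted test holds its level.

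**Step 4: not quantified.** Time to ICU and ICU stay were not simulated. Eligibility includes patients already on an ICU ward, who cannot contribute an ICU entry, so the range of day-0 status among those at risk is narrower for that outcome.

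**The case against.** The section calls itself a summary and leaves further detail to the SAP, and covariates for secondary models are typical SAP detail. The list is plainly not a full covariate specification, since the period adjustment promised for all analyses is not repeated in it, even for the primary model. This has some force: a reader might infer that the Cox and subdistribution models contain no covariates at all, and the documents do not support that. It does not dispose of the point. The list says item by item where day-0 status enters, and it names the log-rank and Gray's tests as the comparisons. As named, neither carries any adjustment, including the one for period.

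Severity is also addressed by presenting outcomes separately for mild/moderate and severe disease {12} and by subgroup analyses {20b}. Those show whether the effect varies with severity; they do not recover power in the overall comparison.

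Three stronger readings are tempting and should not be drawn.

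- That the unadjusted results are wrong or biased. Under randomisation the tests are valid, and a marginal hazard ratio nearer 1 is a different estimand, not an error.
- That mortality in particular loses appreciable power. It does so here only if day-0 status is strongly prognostic.
- That every other efficacy analysis is adjusted. The Wilcoxon comparisons of NEWS and of oxygen and ventilation durations are not, so the contrast holds for the models only.

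**Conclusion.** The point holds as one of efficiency and consistency in exploratory secondary outcomes. Day-0 status is a stated covariate in the primary, cumulative-status and proportional odds models, and is absent from the stated comparisons of mortality, discharge, ICU and length of stay. No other section closes the gap.

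At 258 patients the gain from adjustment is about 2 to 24 points of power for discharge-type outcomes, when each category multiplies the discharge hazard by 0.8 down to 0.4. For mortality it is about 0 points up to a hazard ratio of 2 per category and about 9 points at 3. With no prognostic effect there is nothing to gain.

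These sizes rest on an assumed baseline mix, event rates and treatment effects, on a day-0 effect that follows the fitted linear form, and on ignoring competing death although the planned discharge analysis is a competing-risk one. They indicate a range and do not predict this trial. The primary analysis and its sample size are untouched.

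**What to change.** In {20a}, and correspondingly in the SAP, before database lock:

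- Add day-0 clinical status as a covariate to the Cox model for mortality and to the Fine and Gray models for time to discharge, time to ICU and hospital or ICU stay, alongside the period adjustment promised in the sample size section. State its form. A linear score costs one parameter, which suits mortality: under the assumptions above with no day-0 effect, about 86 × 0.20 + 172 × (1 − 0.80^0.5) = 17 + 18 = 35 deaths would be expected.
- Take the p-value from the adjusted model. Keep the unadjusted log-rank and Gray's tests, shown with the curves, as supportive.
- State that the adjusted hazard ratio is a conditional estimate, as in the primary model.
- For time to ICU, state how patients already in ICU on day 0 are handled.

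The cost is wording and one covariate in models already planned. The value is already collected. Fixing it in advance also removes any choice between adjusted and unadjusted results after the statistician is unblinded.
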